### Terminating Study Criteria

The terminating study criteria are as follows:

- Patients are unable to undergo surgery for various reasons after enrollment (reasons need to be recorded);- The researchers consider that the patients are not suitable to continue the clinical trial (the reason for withdrawal should be recorded);- Patients with serious complications or unbearable adverse reactions;- Patients request that the trial be terminated;- Patients violated the treatment principles (violation of injection and discharge standards, disobedience to the study chemotherapy arrangement, etc.)

We will terminate the study for individual patients once they meet the termination criteria and their data will not be included in the final analysis. Other patients who meet the criteria for admission but do not meet the criteria for termination will continue to participate in our study.

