### Randomization Procedure

Eligible participants will be randomly designated to either the test group or the control group in a 1:1 distribution ratio. First, all enrolled patients were tested the molecular profile of the tumors, such as HER2, PDL1, MSI and MMR expression. And after the patient underwent molecular profile testing, patients with HER2-positive advanced gastric cancer were excluded since trastuzumab in combination with chemotherapy has become the standard treatment for these patients. For the rest of the other patients, follow up treatment protocols could be adjusted according to the patients’ molecular profile, such as immunotherapeutic antibody PD-1 or PD-L1, and so on. Accordingly, in the statistical analysis of data, different patients also need to conduct subgroup hierarchical analysis according to the molecular detection results of tumors to reduce data error. Biostatisticians not involved in this study will use SAS software 9.2 (SAS Institute, Cary, NC, USA) to generate random sequences. A research assistant not participating in the recruitment process will seal the random list in sequentially numbered nontransparent envelopes stored in a cabinet that is double-locked. The research assistant will store the randomly assigned envelopes separately. Data collection and data analysis will be blinded, except that the intervention is not blinded to participants and clinicians (16).

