### Treatment Protocols

All eligible patients will be randomly divided into a test group or a control group according to a 1:1 distribution ratio. The test group will receive D2 gastrectomy plus liver radiofrequency plus postoperative chemotherapy. In the test group, only open surgery is allowed. The control group will receive chemotherapy alone. The chemotherapy regimens of the two groups are the same (11), S-1 plus cisplatin. S-1 will be given orally 80-120 mg/m² per day for the first 3 weeks of every 5-week cycle. The dose of S-1 will be given according to the patients’ body surface area (less than 1.25 m², 80 mg; 1.25–1.5 m², 100 mg; and greater than 1.5 m², 120 mg). Patients will receive cisplatin 60 mg/m² on Day 8 of every 5-week cycle *via* intravenous infusion. **Table 1** shows the treatments applied in this study. **Table 2** shows the medication and usage in this experiment. Because all enrolled patients are tested for the molecular profile of the tumors, such as HER2, PDL1, MSI and MMR expression, follow up treatment protocols could be adjusted according to the patients’ molecular profile, such as trastuzumab or immunotherapeutic antibody. Accordingly, in the statistical analysis of data, different patients also require conduct subgroup hierarchical analysis according to the molecular detection results of tumors to reduce data error.

**Table 1 T1:** The treatments applied in this study.

	gastrectomy (total gastrectomy, distal or proximal gastrectomy plus D2 lymph node dissection)	liver radiofrequency	chemotherapy (S-1 + cisplatin)
test group	√	√	√
control group	—	—	√

**Table 2 T2:** The medication and usage in this experiment.

Chemotherapy drugs	dose	Timing of the drugs (a total of 35 days/cycle)			
		Day 1-7/cycle	Day 8/cycle	Day 9-21/cycle	Day 22-35/cycle
S-1	80-120 mg/m² (oral)	√	√	√	—
cisplatin	60 mg/m² (intravenous infusion)	—	√	—	—

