### Study Endpoints

In this study, the primary endpoint will be the OS. The secondary endpoints PFS and total complication rate. The total complications will include postoperative and chemotherapy complications. Postoperative complications were defined as events occurring within 30 days after the procedure, the severity of which was assessed by the ClavienDindo classification system (23, 24). Postoperative complications will include surgical site infection (SSI refers to the infection that occurs in the incision, deep organ or cavity during the perioperative period. It is mainly divided into superficial wound tissue infection, deep wound tissue infection and organ/cavity infection); anastomotic leaks and duodenal blow-out (identified clinically or radiographically); Chylous fistula (defined as milky white liquid in peritoneal drainage fluid after the start of enteral nutrition); respiratory complications (defined as clinical manifestation of pneumonia or bronchopneumonia confirmed by computed tomographic scan); and other complications (such as: delayedgastricemptying, intestinal obstruction, anastomotic and/or abdominal bleeding, abdominal abscess, pancreatic fistula, pancreatitis and so on.). Postoperative mortality was defined as all-cause death occurring within 30 days after the procedure. Chemotherapy complications refer to the side effects of chemotherapy, such as ototoxicity and nephrotoxicity. For those patients delayed postoperative systemic radiotherapy and/or chemotherapy after 4 weeks of surgery due to surgery and its complications, their clinical data were recorded in detail and analyzed by subgroup stratification.

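### Patients who meet a termination criterion after randomisation are removed from the final analysis, so overall survival is not compared between the randomised groups; bias towards surgery is likely, but its direction and size cannot be derived

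*Protocol article*

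**What the plan says.** Terminating Study Criteria names five grounds:

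- "Patients are unable to undergo surgery for various reasons after enrollment";
- "The researchers consider that the patients are not suitable to continue the clinical trial";
- "Patients with serious complications or unbearable adverse reactions";
- the patient's own request;
- violation of the treatment principles, including not following the chemotherapy arrangement.

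The consequence is that the trial ends for such patients "once they meet the termination criteria and their data will not be included in the final analysis".

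Other sections bear on this:

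- Treatment Protocols: "The control group will receive chemotherapy alone", and both arms get the same S-1 plus cisplatin regimen.
- Randomization Procedure: "the intervention is not blinded to participants and clinicians".
- Clinical Data, Table 3: group determination falls in the pre-operation stage.
- Study Endpoints: OS is primary; PFS and the total complication rate are secondary. "The total complications will include postoperative and chemotherapy complications". Postoperative complications are graded, and 30-day postoperative mortality is defined.
- The adverse-event text that follows Study Endpoints requires every serious adverse event to be reported, whatever its cause.

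The article nowhere states an intention-to-treat or all-randomised analysis.

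**The concern.** The rule merges two separate decisions: stopping participation, and removing data from the analysis. The second is made on events after allocation that are related to prognosis or are themselves outcomes.

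A test patient who deteriorates before the operation is deleted, while the comparable control stays in and the death counts. A patient who dies of an operative complication has met a termination criterion and, as written, leaves the primary OS analysis. One criterion is a judgement by unblinded clinicians, so deletion can also depend on knowledge of the arm.

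At stake are the validity of the primary comparison and the meaning of the complication endpoint, which loses the patients with its most serious events.

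**Working it through.** **1. Does the rule act after randomisation?** Yes, for most of it. Table 3 places group determination before surgery. Serious treatment complications and departures from the chemotherapy arrangement can only follow allocation. Inability to undergo surgery is defined as arising after enrolment.

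**2. Which arm does each criterion reach?** Inability to undergo surgery: test arm only, since controls have none planned. Investigator judgement, serious complications or intolerable reactions, patient request and treatment violation: both arms, since both receive the same chemotherapy.

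**3. Is there a figure in the plan to reproduce?** No expected deletion rate is given. The nearest figure is the margin between 178 required and 200 planned: 200 − 178 = 22 patients, 22/200 = 11%, meant for loss to follow-up. The point does not rest on 178.

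**4. Illustration for OS.** Log-rank simulations with no true difference and 100 patients per arm (from the document). The false-positive rate is the share of runs with Z < −1.96, nominally 2.5%. Not in the document, hence assumed: prognosis, deletion rates and length of follow-up.

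- Set A: 1,500 runs per scenario. Poor-prognosis patients are 10% or 20% of each arm, with median OS 4, 6 or 8 months against 14 for the rest (hazard 14/4 = 3.5 to 14/8 = 1.75 times higher). All are deleted from the test arm only. Censoring at 36–60 months.
- Set B: 3,000 runs per scenario. Accrual 24 months (November 2020 to November 2022), then 36 months' follow-up. 20% of each arm has poor prognosis, with hazard 2 or 3 times that of the rest (median 14 months). Deletions are drawn from these patients at the stated share of each arm.

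In set B, U = Σ(a − q) and V = Σq(1 − q) over events, where a marks a test-arm event and q is the test-arm share at risk. Z = U/√V, and HR = exp(mean of U/V).

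| Deleted, test / control | Set A: HR; false positives favouring surgery | Set B: HR; same |
|---|---|---|
| none (all randomised) | 2–3% (rate only) | about 1.00; 2.1–3.1% |
| 5% / 0 | – | 0.97–0.98; 3.7–4.3% |
| 10% / 0 | 0.92–0.96; 4.8–7.2% | 0.94–0.95; 5.1–6.2% |
| 15% / 0 | – | 0.90–0.92; 8.4–10.3% |
| 20% / 0 | 0.85–0.90; 9.9–18.9% | 0.86–0.90; 9.8–15.7% |
| 15% / 5% | – | 0.92–0.95; 6.0–7.4% |
| 10% / 10% | – | about 1.00; 2.6% |
| 5% / 15% | – | 1.06–1.08; 0.9–1.3% |

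Plausibility check: with 20% of controls at three times the hazard and none left in the test arm, the hazard ratio at the start is 1/(0.8 × 1 + 0.2 × 3) = 1/1.4 = 0.71. It moves towards 1 as the poor-prognosis controls die, which fits an average of 0.86.

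**5. Illustration for complications.** If the true rate is p and patients with serious complications (all counted in p) make up a share s of the arm, the analysed rate is (p − s)/(1 − s). Take p = 9/11 = 81.8%, the sample-size section's count of adverse events with gastrectomy plus chemotherapy, used only as a level:

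- s = 10%: 0.718/0.90 = 79.8%
- s = 20%: 0.618/0.80 = 77.3%
- s = 30%: 0.518/0.70 = 74.0%

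The total rate moves modestly, but no serious complication remains in the analysed set. The surgery criterion works the other way: if 10% of the test arm were never operated on and, at the extreme, none had a complication, the analysed rate would rise to 0.818/0.90 = 90.9%.

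**6. Sections side by side.** Study Endpoints counts complications of every grade and defines 30-day mortality, and the adverse-event text reports all serious events. Terminating Study Criteria removes from the final analysis patients who had them. The sections cannot all be applied as written.

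**The case against.** A reader might infer that the rule deletes poor-prognosis patients mainly from the surgical arm and so favours surgery for certain. The document does not support that. Four of the five criteria apply to controls too, and chemotherapy toxicity or non-adherence could remove many of them. Equal deletion leaves the HR near 1, and a reverse imbalance works against surgery. The larger figures need deletion from the test arm alone and a much worse prognosis in those deleted; neither is stated anywhere. This objection stands against any claim about sign or size.

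A second tempting reading is that the surgical complication rate must come out too low. That does not follow either: deleting never-operated patients can raise the test-arm rate, and serious toxicity is deleted from controls as well. Nor would serious events go unreported, since safety reporting covers them all. The fault is a conflict between sections.

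The surgery criterion may also bite less than it seems. Entry requires operative staging with lavage cytology and no contraindication to treatment. Randomization Procedure uses the word enrolled for patients still awaiting HER2 exclusion, so some failures after enrolment may precede allocation, where exclusion does no harm. This narrows one criterion and leaves the others untouched.

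Finally, an analysis plan may exist. It could add detail, but an all-randomised analysis would contradict this explicit sentence, so the sentence itself has to change.

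**Conclusion.** The rule is wrong as written. It excludes randomised patients on outcome-related and partly discretionary events in a trial where clinicians are not blinded, and it sets the primary analysis at odds with the trial's own complication endpoint and safety reporting. This rests on the text alone and needs no assumption.

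Bias in favour of surgery is likely, because one criterion can operate only in the test arm, but this is not proven. The size is unknown. Under the assumptions shown, the apparent HR with no true effect runs from about 0.85 (20% deleted from the test arm alone) to 1.08 (5% of test and 15% of control deleted). The matching false-positive rate in favour of surgery runs from about 19% down to about 1%. A mixed case of 15% test and 5% control gives 0.92–0.95 and 6–7%. Analysing all randomised patients keeps it at 2–3%. These figures show sensitivity to the rule and do not forecast the result.

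**What to change.** In Terminating Study Criteria, delete the clause that takes these patients' data out of the final analysis, and state instead that:

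- OS and PFS are analysed in all randomised patients, in the arm allocated;
- meeting a termination criterion does not by itself end outcome follow-up or remove data already collected;
- patients who withdraw consent to follow-up are censored at last contact, not deleted;
- complications and deaths are counted in all patients who started treatment, including those who stopped because of a complication.

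Keep the present exclusion at most as a labelled per-protocol sensitivity analysis. Reconcile the section with Study Endpoints and the adverse-event text. The clinical rules on when treatment stops need not change and are left as they stand.

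The cost is wording, continued survival follow-up of patients who stop treatment, and a possibly less favourable estimate. No extra patients are needed for this change.

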### Randomization Procedure

Eligible participants will be randomly designated to either the test group or the control group in a 1:1 distribution ratio. First, all enrolled patients were tested the molecular profile of the tumors, such as HER2, PDL1, MSI and MMR expression. And after the patient underwent molecular profile testing, patients with HER2-positive advanced gastric cancer were excluded since trastuzumab in combination with chemotherapy has become the standard treatment for these patients. For the rest of the other patients, follow up treatment protocols could be adjusted according to the patients’ molecular profile, such as immunotherapeutic antibody PD-1 or PD-L1, and so on. Accordingly, in the statistical analysis of data, different patients also need to conduct subgroup hierarchical analysis according to the molecular detection results of tumors to reduce data error. Biostatisticians not involved in this study will use SAS software 9.2 (SAS Institute, Cary, NC, USA) to generate random sequences. A research assistant not participating in the recruitment process will seal the random list in sequentially numbered nontransparent envelopes stored in a cabinet that is double-locked. The research assistant will store the randomly assigned envelopes separately. Data collection and data analysis will be blinded, except that the intervention is not blinded to participants and clinicians (16).

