### Inclusion Criteria

Patients will be included when they meet all of the following conditions:

- Patients who are male or female, aged 20 to 75 years;- Patients who were diagnosed histologically with primary gastric adenocarcinoma;- Patients diagnosed with clinical T1–3 disease by laparotomy or laparoscopy (for T1-T3 patients with the node positive, in order to eliminate the inter group differences, they were randomly divided into control group or experimental group according to the clinical nodal status (further subgroup: N0–1 vs N2–3). For patients with para-aortic lymph node metastasis above the coeliac axis or below the inferior mesenteric artery (lymph node 16a1/b2 of maximum diameter ≥1 cm), or both, or T4 patients with the node positive, according to the NCCN diagnosis and treatment guidelines for gastric cancer and the recommendations of our multidisciplinary diagnosis and treatment team, neoadjuvant therapy was first chosen) (11);- Patients who will undergo diagnostic laparoscopic exploration combined with peritoneal lavage cytology to exclude peritoneal disseminated implant metastasis that is not visible to the naked eye (14);- Patients who will be examined for the molecular profile of the tumors (HER2, PDL1, MSI and MMR expression) [patients with HER2-positive advanced gastric cancer were excluded since trastuzumab in combination with chemotherapy has become the standard treatment for these patients (15)];- Patients with distant metastases that were limited to synchronous liver metastases confirmed by both laparotomy and CT scan;- Patients with metastatic liver tumor ranging from 2 to 4 with tumor diameters ranging from 1 cm to 5 cm (11) (In order to avoid the omission of potential liver metastases, we used contrast-enhanced liver ultrasound as one of the means of further screening. Considered that unless data are now available from ongoing trials, ablation for resectable liver metastasis lesions should not be used in radiofrequency of liver resection. We recommend all patients to multidisciplinary tumor boards to determine whether the liver metastasis is actually unresectable);- Patients whose PS (performance status) was from 0 to 1;- Patients who have not previously been treated for gastric cancer other than EMR;- Patients who have not previously received radiation therapy or chemotherapy for any other malignancy;- Patients who have no contraindications to treatment (surgery, radiofrequency ablation, and chemotherapy);- Patients and their families voluntarily participated in the study and signed the informed consent form.

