To verify the comparison of the efficacy of D2 gastrectomy plus liver radiofrequency plus postoperative chemotherapy versus chemotherapy alone for patients with GCLM, we designed a superiority study with a superiority margin of 5% (α= 0.05, β= 0.20, 80% power). With a standard error of 0.05 and a confidence interval of 80%, a sample size of 178 is necessary. To minimize sampling error and account for the rate of loss to follow-up for various reasons, we determined the sample size to be 200 participants. Standard descriptive statistics will be used to analyze qualitative and quantitative variables such as relative and absolute frequencies, frequency tables, means, medians, standard deviations, ranges, and quartiles. A 95% confidence level will be considered appropriate for analysis. Descriptive statistics will also be used to describe the most relevant clinical parameter measurements. Analysis of categorical variables will be performed by two-sample t tests or Fisher’s exact test. If there is no significant difference in the response rate to D2 gastrectomy plus liver radiofrequency plus postoperative chemotherapy versus chemotherapy alone, then the result will be negative, that is, the difference is not related to whether to apply the treatment strategy of D2 gastrectomy plus liver radiofrequency plus postoperative chemotherapy for patients with GCLM; otherwise, there is a relationship.

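### Allocation is said to follow clinical nodal status (N0–1 vs N2–3), but the randomisation section names no strata and no named analysis uses nodal status, so the intended balance is not secured

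*Protocol article*

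**What the plan says.** The nodal factor appears only inside a parenthesis in the Inclusion Criteria. For T1–T3 patients with positive nodes, that text says they are "randomly divided into control group or experimental group according to the clinical nodal status (further subgroup: N0–1 vs N2–3"). The reason given is "in order to eliminate the inter group differences".

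The Randomization Procedure describes how allocation is done: "Eligible participants will be randomly designated to either the test group or the control group in a 1:1 distribution ratio". Biostatisticians outside the study use SAS "to generate random sequences", and a research assistant will "seal the random list in sequentially numbered nontransparent envelopes". Nodal status is not mentioned there. The opening paragraph of Methods/Design and the Treatment Protocols section also give only the 1:1 ratio.

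On analysis, the Randomization Procedure and Treatment Protocols call for "subgroup hierarchical analysis according to the molecular detection results of tumors". Study Endpoints adds a subgroup analysis of patients whose postoperative treatment is delayed beyond four weeks. The only comparative tests named are in Sample Size Estimate and Statistical Analysis: "Analysis of categorical variables will be performed by two-sample t tests" or by Fisher's exact test. None of these places refers to nodal status.

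**The concern.** Nodal status is the one factor that the article says governs allocation. A site working from the Randomization Procedure would find no instruction to establish the nodal stratum before drawing an envelope, and no second series to draw from. If there is in fact a single series, balance on this factor is left to chance.

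The strata are also awkward as written. The clause covers node-positive patients, but the lower stratum is N0–1. Node-negative T1–T3 patients meet the T-stage criterion and are not clearly covered.

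The trial should be analysed by the groups within which it randomises. If allocation is stratified on a prognostic factor and the survival test ignores it, the test's variance is too large for the design. The type I error then falls below nominal and some power is lost.

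**Working it through.** **1. The article's own figure.** There is no stated figure on nodal balance to reproduce. The sample size of 178 (raised to 200) does not involve nodal status. A pooled one-sided two-proportion calculation on 60% vs 81.8% with a 5% margin comes within 3% of it:

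n per arm = 2 × 0.709 × 0.291 × (1.645 + 0.842)² / (0.818 − 0.60 − 0.05)² ≈ 91, or 182 in total.

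Stratifying the randomisation changes neither 178 nor 200.

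**2. The texts side by side.**

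| Section | Nodal status used? | What it gives |
|---|---|---|
| Inclusion Criteria | Yes, N0–1 vs N2–3 | Factor and purpose, no mechanism |
| Randomization Procedure | No | 1:1, sequences, list, numbered envelopes |
| Treatment Protocols | No | 1:1; analysis by molecular profile |
| Sample Size Estimate and Statistical Analysis | No | t tests, Fisher's exact test |
| Study Endpoints | No | Analysis by delayed postoperative treatment |

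**3. Chance imbalance if there is one unstratified list.** The input from the article is 100 patients per arm. The N2–3 share p is assumed, because the article gives none.

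SD of the difference between arms = √(p(1 − p) × 2/100)

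- p = 0.5: √(0.25 × 0.02) = 7.1 points, 95% range ±13.9.
- p = 0.3: √(0.21 × 0.02) = 6.5 points, 95% range ±12.7.

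The exact (hypergeometric) chance of a gap of at least 10 points is 16%, 20% and 16% for shares of 30%, 50% and 70%.

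**4. Effect on the OS test.** This was simulated with 4,000 trials per setting. All inputs except N = 200 are assumptions: exponential survival, control median 14 months, 36 months of follow-up for each patient, half of patients N2–3, treatment HR 0.65, two-sided 5% level. Stratified allocation means near-exact balance within each stratum.

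| Nodal HR | Allocation | Power, unstratified log-rank | Power, stratified log-rank |
|---|---|---|---|
| 1.0 | stratified | 74.2% | 74.2% |
| 1.5 | single list | 76.7% | 77.7% |
| 1.5 | stratified | 77.3% | 78.5% |
| 2.0 | single list | 73.1% | 79.6% |
| 2.0 | stratified | 73.7% | 79.2% |
| 3.0 | single list | 64.5% | 79.4% |
| 3.0 | stratified | 66.5% | 80.5% |

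The Monte Carlo standard error is about √(0.75 × 0.25/4000) = 0.7 points per entry.

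Reading across a row gives the effect of the analysis: about 1 point at nodal HR 1.5 and, after stratified allocation, 79.2 − 73.7 = 5.5 points at nodal HR 2. Comparing the two rows for one nodal HR gives the effect of the allocation method: at most 66.5 − 64.5 = 2 points.

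**5. Type I error of the unstratified test after stratified allocation.** It is 5.0% at nodal HR 1.5, 3.9% at 2 and 2.7% at 3. The stratified test stays between 4.9% and 5.3%.

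**The case against.** The strongest answer is that the two sections can be read together. The Inclusion Criteria supply the factor and the Randomization Procedure supplies generation and concealment. The plural in "to generate random sequences" is compatible with one sequence per stratum, and a stratified list is still a list in numbered envelopes. This stands to the extent that the article is silent on strata in the Randomization Procedure and never calls the list unstratified. A reader might infer that there is one unstratified list and that balance has been lost, but the text does not establish that. What remains is that this section goes into detail on software, personnel, concealment and storage, yet omits the factor said to govern allocation.

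Second, whether the OS test is stratified is commonly settled in a statistical analysis plan, and none is shown. This also stands. The article names no survival test of any kind, and the sentence on t tests concerns categorical variables. It is therefore not evidence of a planned unstratified OS comparison, and the missing test is not itself counted as an error here.

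Third, the article promises balance only. A reader might speak of a promised gain in precision, but none was promised. Nor should the power differences be charged to the envelope list, since nearly all of the gain comes from the analysis.

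Fourth, a stratum labelled N0–1 includes N0 by name, so the place of node-negative patients can be guessed. That is fair. It is a drafting conflict that one phrase resolves.

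**Conclusion.** The point holds as an inconsistency to be reconciled. The Inclusion Criteria say that allocation follows nodal status, the Randomization Procedure does not provide for it, and the factors named for analysis leave it out. Balance on nodal status is therefore not secured by the text, which is less than saying it is lost.

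If there is one list, the chance difference has an SD of about 7 points with half of patients N2–3. This is ordinary random variation and not bias. If allocation is stratified, an OS comparison that ignores the stratum is conservative and gives up about 1 point of power at nodal HR 1.5 and 5 to 6 points at nodal HR 2. These power figures illustrate assumed values for nodal HR, treatment HR, median survival and N2–3 share. None of those values comes from the article. A larger loss appears only with a stronger assumed nodal effect.

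The correction should be made because it is cheap and because the stratified analysis is sound under either reading of the randomisation text.

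**What to change.** 1. In the Randomization Procedure, state that randomisation is stratified by clinical nodal status, N0–1 (including node-negative) vs N2–3. Provide one blocked list and one numbered envelope series per stratum, with the stratum recorded before the envelope is drawn.
2. In the Inclusion Criteria, remove the restriction of the strata to node-positive patients, or point to the Randomization Procedure, so that the two sections agree.
3. In Sample Size Estimate and Statistical Analysis, or in the analysis plan, compare OS and PFS by a log-rank test and a Cox model stratified by N0–1 vs N2–3. Use the clinical status recorded at randomisation, since the control group has no gastrectomy and hence no surgical nodal staging to match the test group's.

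The cost is a second envelope series and a few sentences of text. The sample size does not change. If envelopes have already been used, the article should report how they were prepared. Item 3 still applies and costs nothing: in the simulation, stratifying made no difference to power when nodal status had no effect on survival.
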